## Abstract

**Introduction:**

Chronic dyspnoea is a prevalent symptom, and primary care is ideally placed to identify and manage it. However, chronic dyspnoea is under-reported by patients and can be a diagnostic dilemma for practitioners. A fully automated system of patient screening, coupled with a clinical decision support system (CDSS) that uses a validated and evidence-based dyspnoea algorithm, may improve detection, diagnosis and management of the condition. There is currently no CDSS validated for chronic dyspnoea diagnosis and management in primary care in Australia. The objectives of this study are to assess the clinical impact of a CDSS for chronic dyspnoea in primary care. We hypothesise that the use of the CDSS will lead to a clinically significant improvement in patient-reported dyspnoea scores, reduced time to diagnosis and healthcare costs at 12 months compared with standard care.

**Methods and analysis:**

The BREATHE study is an open-label, cluster-randomised controlled trial of standard of care compared with a CDSS. General practices (n=40) in metropolitan, regional/rural and rural/remote settings will be recruited and randomised equally to pre-screening for chronic dyspnoea and usual standard-of-care management or pre-screening *and* CDSS-guided management. The CDSS includes an algorithm derived from a robust data and clinical knowledge model and incorporates evidence-based recommendations for the assessment and management of chronic dyspnoea. It is integrated into general practice medical software systems, fitting in the workflow of general practitioners (GPs). Eligible patients will be ≥18 years old and will have previously consented to receive SMS communication from their practice. In-scope patients will receive an automated text message prior to their GP appointment and will be screened for chronic dyspnoea (≥4 weeks). Patients identified with chronic dyspnoea will be invited to participate in the BREATHE study and followed up for 12 months. The primary outcome is improvement in the Dyspnoea-12 (D-12) score from baseline to 12 months, measured by the Dyspnoea-12 (D-12) questionnaire. Secondary outcomes include disease-specific questionnaires to assess changes in clinical outcomes, time to final diagnosis, quality of life, healthcare utilisation and costs incurred to patients.

**Trial registration number:**

The trial is registered at ANZCTR (ACTRN12624001451594). ANZCTR is a primary registry that meets the requirements of the ICMJE and is listed on the ICTRP Registry Network.

**Ethics and dissemination:**

The study protocol has been approved by the University of New South Wales Human Research Ethics Committee (HREC) (iRECS6645) and complies with the National Health and Medical Research Council ethical guidelines. Participating practices and each GP will provide written, informed consent. All patients being screened will provide electronic informed consent. Results of the study will be disseminated through various forums, including peer-reviewed publications and presentation at national and international conferences. Following the study, participating practices will be provided with a summary of the findings of the study, together with a full copy of any publications and a plain language statement for participants, which will be made available in the practice reception area.

STRENGTHS AND LIMITATIONS OF THIS STUDYThe clinical decision support system (CDSS) for breathlessness uses an evidence-based algorithm based on routinely collected data from a large UK general practice database and is integrated within existing primary care data systems and workflow.The CDSS incorporates an algorithm developed using Bayesian Networks to predict twenty two conditions associated with presentations of breathlessness, ascertained by analysis of the data from 384 994 episodes of breathlessness recorded in the database. It uses probabilities to identify the highest likely cause of dyspnoea and delivers the latest evidence-based preventive care tailored for each patient depending on their history and presenting symptoms.The study is a pragmatic cluster randomised trial of 40 general practices including metropolitan, rural and remote sites ensuring the outcomes are representative of the Australian population.A current limitation is the integration with a single practice software system (Best Practice); however, this serves as a proof-of-concept, with future work planned for broader implementation.The use of a tool that requires SMS communication may introduce bias by excluding older, less technologically adept or non-English-speaking participants; however, using an established system within the GP workflow was vital as a proof of concept.

## Introduction

 Dyspnoea is a common presenting complaint in primary care, experienced by approximately 10% of Australians.^1^ It can be a symptom of cardiorespiratory disease, obesity, deconditioning, anxiety or a combination of factors/conditions.^2^ The development and implementation of approaches for the early and accurate detection and diagnosis of these conditions are a major unmet need. An estimated 70% of people with asthma or chronic obstructive pulmonary disease (COPD) remain undiagnosed and hence untreated in the community.^3^,^5^ Dyspnoea is complex but is often overlooked and under-recognised by patients. Research indicates that there is significant potential to support general practitioners (GPs) in enhancing screening and risk stratification for dyspnoea, helping to ensure earlier and more accurate identification of underlying conditions.^6^

GPs see at least 85% of the Australian population annually and are ideally placed to screen and manage dyspnoea; however, their provision of optimal assessment is often constrained by time pressures during patient consultations, and there are large gaps between guidelines and practice. Most GP presentations for dyspnoea are for acute episodes.^7^ Once the acute presentation has been addressed, there is often little, or no time left, to address underlying causes and management for chronic dyspnoea.

Our focus groups with GPs, specialists and allied health^8^ found that while GPs are crucial to achieving optimal care of breathless patients, the multifactorial nature of dyspnoea^2^ is a diagnostic and management challenge that limits their ability to provide the correct diagnosis or best management.^6^ New approaches are needed to reduce avoidable diagnostic tests and potentially harmful and unnecessary treatments. The gaps in care across common problems, such as asthma, COPD, cardiac failure, obesity or lifestyle issues such as deconditioning,^2^ highlight the need for integrated strategies to manage the multifactorial causes of dyspnoea^9^ in a person-centred^10^ and evidence-based way.^11^

The Breathlessness Rapid Evaluation And ThErapy (BREATHE) clinical decision support system (CDSS) is an innovative digital technology that is integrated into GP electronic medical record systems and embeds a clinical algorithm for the diagnosis and management of dyspnoea. It provides personalised treatment recommendations for the most common causes of dyspnoea identified in our previous analysis of Australian GP records,^12^ including asthma, COPD, heart failure, lower respiratory infections, pulmonary emboli and contributors such as obesity, deconditioning and anxiety.

The BREATHE CDSS study is partnering with the BREATHE SMART project, conducted by the University of Notre Dame (ACTRN12624001455550), which uses a pre-consultation screening tool as the primary mechanism to identify eligible patients with unrecognised breathlessness (see figure 1). The BREATHE SMART screening tool and the BREATHE CDSS are incorporated into a current workflow of pre-screening via a smartphone SMS (BetterConsult) which will identify eligible participants to consent to the BREATHE randomised controlled trial through the use of the modified Medical Research Council (mMRC)^13^ breathlessness scale. Once detected, a more efficient approach to incorporating evidence-based dyspnoea clinical decision support for the GPs to diagnose and manage patients is required. The use of CDSS has been shown to improve diagnosis and treatment in other diseases,^14^,^17^ although CDSS tools must be tested for their accuracy and potential for benefit over harm in each clinical context.^18^,^20^ There are very few validated dyspnoea algorithms, and none have been tested in the Australian primary care setting or integrated within the GP practice data systems or workflows.^21^ A CDSS would assist GPs in navigating the multiple possible causes of dyspnoea and deliver the latest evidence-based preventive care tailored for each patient.

**Figure 1 F1:**
[figure not shown]
Flow of BREATHE SMART and BREATHE CDSS protocols illustrated. BREATHE, Breathlessness Rapid Evaluation And ThErapy; CDSS, clinical decision support system; GP, general practitioner.

The BREATHE study will use our CDSS prototype in a cluster randomised clinical trial in primary care with the aim to improve diagnostic accuracy, symptom management, clinical outcomes and diagnostic efficiency of chronic dyspnoea compared with standard clinical practices. Assessment will focus on clinical and patient-reported outcomes, clinician uptake and health economic impacts.

## Methods and analysis

### Practice recruitment

40 urban, regional and rural GP practices will be recruited across Australia with the assistance of our GP investigators and collaborators: HealthShare (BetterConsult software) and Ochre Health, and through advertising the project via newsletters from the Royal Australian College of General Practitioners (RACGP) and the Primary Health Networks and at GP meetings.

### Eligibility

General practice

Use BetterConsult software.^22^Provide written informed consent to participate (online supplemental file 1).

All general practitioners

Provide written informed consent to participate (online supplemental file 2).

Participants

Aged ≥18 years.Consent to text message (SMS) communication with their GP practice.Dyspnoea lasting ≥4 weeks.Provide electronic informed consent (e-consent) to participate (onlinesupplemental files 3  4).

### Intervention

The BREATHE CDSS incorporates a data- and clinical-driven algorithm for diagnosis of breathlessness: the data model embedded in the CDSS has been developed and validated through in-depth statistical analyses of a large GP database from the UK (>1000 practices)^23^ and uses a Bayesian Network^24^ approach to calculate posterior probabilities for each of the 22 potential diagnoses based on the integrated input of patient demographics, pre-screening symptom data, GP-entered physical examination findings and historical data extracted from the electronic medical record (eMR).^25^ Bayesian Network CDSS tools are gaining popularity because of their ability to be flexible with respect to disparate data and their open box approach.^26 27^ The data-driven model was overlaid with a clinical knowledge model. The 22 relevant diagnoses for breathlessness that the CDSS can detect, and the component that contributes to each, are summarised in table 1. The integration of the two components ensures that the BREATHE CDSS probabilities are clinically appropriate and supported by data. Importantly, it recommends cost and time-effective diagnostic tests and provides links to evidence-based guidelines and patient resources for each provisional diagnosis to align management with best practice guidelines and to enable GPs to provide patients with additional patient-based resources. This clinical algorithm was incorporated into an existing medical software platform already in place in a large proportion of Australian primary care networks (BetterConsult) to ensure translation into practice via existing workflows.

**Table 1 T1:** Components of the models used in the algorithm that contribute to the diagnoses that the Breathlessness Rapid Evaluation And ThErapy clinical decision support system is trained to detect

Relevant diagnosis	Data model	Knowledge model
Anaemia		YES
Anxiety		YES
Asthma	YES	YES
Chronic bronchitis	YES	YES
COPD	YES	YES
Costochondritis		YES
Heart (other)		YES
Heart block or clinically important conduction defect		YES
Heart failure	YES	YES
ILD (pulmonary fibrosis)	YES	YES
Lung cancer	YES	YES
Myocardial infarct/heart attack		YES
Non-infective pneumonitis/infiltrate		YES
Non-pneumonia LRTI	YES	YES
Pneumonia	YES	YES
Pulmonary embolism	YES	YES
Pulmonary hypertension/right heart strain		YES
Rib fracture		YES
Tachyarrhythmia (including Atrial Fibrillation)		YES
VCD		YES
Deconditioning (loss of fitness)		YES
Dysfunctional breathing/breathing pattern disorder	YES	

COPD, chronic obstructive pulmonary disease; ILD, interstitial lung disease; LRTI, lower respiratory tract infection; VCD, vocal cord dysfunction.

### Trial design

The pragmatic implementation trial will be a cluster randomised controlled 2-arm trial (RCT) in 40 primary care sites. Each arm will comprise 20 practices, outlined below:

ARM 1: pre-screening for chronic dyspnoea and standard of care management.

ARM 2: pre-screening for chronic dyspnoea and CDSS guided management

Practices will be recruited from urban, regional and rural areas and individual GPs within each practice will consent to participate. Recruitment of patients will continue for 12 months. We will purposefully sample practices from all categories to ensure representation of each region (metropolitan, regional, rural) is equal in each arm. The randomised ‘units’ in this cluster RCT are the GP practices. The GP practices will be enrolled over time, so the randomisation list will be created by an unblinded statistician and (blinded to the study team) include a schedule within each regionality using randomly permuted blocks (a mix of size two or four) to ensure balance, and we will allocate and advise the study team as sites are activated, as GP practice allocation will be unblinded to both the study team and the GP practice.

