### Statistical analyses

The primary outcome is change in D-12 score, which has a minimum clinically important difference of 2.83 (out of a possible score of 36).^37^ Assuming a two-arm parallel cluster trial with a baseline measure, a total of 40 GP practices (clusters) provides 90% power to detect a mean difference in D-12 of four points at 0.05 significance level. To achieve this, each practice will be expected to recruit a minimum of nine participants who will be followed up for 12 months each. Allowing for a drop-out rate of 10%, we aim to recruit 10 participants per cluster for a total of 400 participants. A conservative SD of D-12 of 15 points and individual autocorrelation (the correlation between observations from the same individual at different times) of 0.65 is assumed. These calculations are robust to values of the intra-cluster correlation coefficient up to 0.10.

The primary analysis will compare change in D-12 scores at 12 months between the CDSS and standard care arms. The analysis will be performed using a repeated-measure linear mixed model including measurements taken at baseline, 3, 6 and 12 months. The model will include the effect of the visit, the randomised group and the interaction between randomised group and visit. A random cluster effect will be used to model within-cluster correlation, and a repeated effect will be used to model within-patient correlations.

A similar approach will be used to analyse secondary outcomes with logistic regression used in place of linear regression for binary outcomes. Controlled multiple imputations^38^ will be used to assess the robustness of the primary outcome results to different missing data assumptions. Sensitivity analyses including additional covariate adjustments will also be performed. A detailed statistical analysis plan will be developed and made publicly available before any analysis.

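### Practices are randomised within region, but the stated primary model has no region term; the correction is cheap and the gain probably small

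*Protocol article*

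**What the plan says.** Under Trial design, practices are the randomised units, allocation is equal ("Each arm will comprise 20 practices"), and the list will "include a schedule within each regionality using randomly permuted blocks (a mix of size two or four) to ensure balance". The three categories named there are metropolitan, regional and rural.

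Under Statistical analyses, the primary comparison is change in D-12 at 12 months, from a repeated-measures linear mixed model using baseline, 3, 6 and 12 months. On its fixed effects: "The model will include the effect of the visit, the randomised group and the interaction between randomised group and visit". It adds one random effect for the cluster and a repeated effect within patient. On other covariates: "Sensitivity analyses including additional covariate adjustments will also be performed". Region is not named in either place. A detailed statistical analysis plan is promised before any analysis.

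**The concern.** When randomisation is stratified, the arms are made alike on the stratum by design, and the usual rule is to analyse as randomised, with the stratum in the primary model. Here the stratification factor is absent from the listed terms, and the only route by which it could enter is a sensitivity analysis that does not name it.

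Two things are at stake. First, if region affects change in D-12, a practice-level standard error that ignores region does not credit the balance that the design bought, so the test is somewhat conservative. Second, if the unadjusted primary result and the region-adjusted sensitivity result differ, the one that follows the design would be the secondary one. With 40 practices, incomplete permuted blocks, unequal practice sizes and drop-out can also leave some regional imbalance that the primary model would not correct.

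**Working it through.** **Inputs from Statistical analyses**

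- Target: "a total of 40 GP practices (clusters) provides 90% power to detect a mean difference in D-12 of four points at 0.05 significance level" (two-sided assumed).
- Cluster size m = 9: "each practice will be expected to recruit a minimum of nine participants". With 20 practices per arm this is 180 analysable patients per arm.
- SD = 15: "A conservative SD of D-12 of 15 points and individual autocorrelation". Individual autocorrelation IAC = 0.65.
- ICC up to 0.10.

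**Assumed, because the article does not give them**

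- Cluster autocorrelation (CAC, the correlation of a practice's effect between visits): 1, 0.9 or 0.8.
- Share R of practice variance in *change* that region explains: 0, 20% or 30%.

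**Step 1. Reproduce the stated power.** For a cluster trial with a baseline measure:

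Var = (2·SD²/180)·[1+(m−1)·ICC]·(1−r²), with r = [m·ICC·CAC+(1−ICC)·IAC]/[1+(m−1)·ICC].

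At ICC 0.10 and CAC 1:

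- r = (0.9+0.585)/1.8 = 0.825
- Var = 2.5 × 1.8 × 0.3194 = 1.437, so SE = 1.199
- power = 0.916 (normal) or 0.902 (t, 38 df)

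Over ICC 0 to 0.10 with CAC 1, power is 0.911-0.916 (normal) or 0.896-0.902 (t). The 90% reproduces, and 360/0.9 = 400. No term in the calculation takes credit for stratification. At ICC 0.10, power falls to 0.83-0.85 with CAC 0.9 and 0.76-0.78 with CAC 0.8, so the stated robustness to ICC 0.10 implies a CAC close to 1.

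**Step 2. Region affects level only, CAC 1.** A region effect that is constant over visits cancels from the change contrast. Mixed models fitted to simulated data (ICC 0.10, region explaining 50% or 25% of practice variance) gave the same 12-month estimate with and without region. The SEs were 1.249 without and 1.251 with region at 50%, and 1.259 and 1.259 at 25%. When region also shifted follow-up by about 2 points per SD of a region score, the SE was 1.259 without region and 1.253 with region-by-visit. These checks used only 8-12 data sets each, with complete data, exact balance and some convergence warnings.

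**Step 3. Region affects change, CAC 0.8, ICC 0.10.** For the change score:

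- practice component P = 2 × 225 × 0.10 × 0.2 = 9
- patient component W = 2 × 225 × 0.9 × 0.35 = 141.75
- ICC of change = 9/150.75 = 0.060
- practice share of the contrast variance = 81/222.75 = 0.364
- SE without region = √[(2/20)(9 + 141.75/9)] = √2.475 = 1.573

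With arms balanced by region, the true variance is (2/20)[9(1−R) + 15.75]. The unadjusted columns below use SE 1.573, that is, an analysis carrying practice-level variance in change but no region.

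| R | True SD | Type I error, unadjusted | Power, unadjusted | Power, adjusted |
|---|---|---|---|---|
| 20% | 1.515 | 0.042 | 0.727 | 0.752 |
| 30% | 1.485 | 0.038 | 0.731 | 0.768 |

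The variance credited falls by 0.364 × 0.20 = 7% to 0.364 × 0.30 = 11%, and the power gain is about 2.5 to 4 points (normal approximation). At CAC 0.9 the gain is 1 to 2 points; at CAC 1 it is nil.

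**Step 4. The same scenario under the model as worded.** A single practice intercept, constant over visits, also cancels from the contrast. The SE is then roughly √[2 × 150.75/180] = 1.294, against a true 1.573 with no region effect, 1.515 at R = 20% and 1.485 at R = 30%. A simulation of 4,000 runs with assumed strata of 14, 14 and 12 practices agrees: true SD 1.545 and 1.479 against model SEs of 1.292 and 1.293, with type I error about 0.098 and 0.086. Adding region-by-visit alone does not repair this. At R = 20% the SE becomes √[2 × (7.2+141.75)/180] = 1.286.

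**The case against.** The strongest reply is that this belongs to the statistical analysis plan. The article says which terms the model will include, not that it will include no others; the covariates left to sensitivity analyses need not mean the design factor; and a full plan is promised. This has some weight and limits the point to a correction that can still be made. It does not remove it: the article itself sets out the terms of the primary model and assigns covariate adjustment elsewhere, so a plan written to match it would leave region out.

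The second reply is that the consequence is slight, and that stands. A reader might infer that the precision gained by stratifying is thrown away. It is not: balance within region lowers the true variance whatever model is fitted, and with balanced arms the adjusted and unadjusted estimates coincide. What can be lost is the credit for it in the reported standard error.

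A reader might also infer that the confidence interval will be too wide. That holds only if the model carries practice-level variance in change. With the constant practice intercept as worded and CAC below 1, Step 4 shows an interval that is too narrow, and leaving out region is not the cause.

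Finally, nothing in the article says that region influences change in D-12, so zero is a realistic value for R.

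**Conclusion.** The mismatch is real: randomisation is stratified by region and the stated primary model is not. Its effect is probably small, and the article gives no figure from which to size it. The gain from including region is about nil if region affects only the level of D-12 and practice effects are stable, which is close to what the power calculation implies. It is about 2.5 to 4 points of power at ICC 0.10, CAC 0.8 and R of 20-30%, all but the ICC being assumed values.

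A much larger loss can be produced. In a practice-level simulation at ICC 0.10 where baseline removed none of the between-practice variance and region explained half of it, power was 0.53 unadjusted against 0.70 adjusted, and unadjusted type I error was 0.016. A reader should not take that as the likely effect, because it sets aside the baseline measure on which the protocol's own calculation relies.

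The stated 90% is unaffected, since it claimed nothing for stratification. The trial is not invalid. The case for acting is that the analysis should follow the randomisation, that it protects against residual regional imbalance, and that it costs almost nothing.

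**What to change.** In the statistical analysis plan, add region and region-by-visit as fixed effects to the primary model, and keep the model without them as a sensitivity analysis. The by-visit term is needed because a region main effect alone cancels from the change contrast.

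In the same edit, state how practice-level variation in change is modelled, for example with a practice-by-visit random effect. Without that, the standard error of the 12-month contrast cannot properly credit the stratification and can be too small.

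The cost of the region terms is one line of the model and about 2 practice-level degrees of freedom (three regions less one). No change to recruitment, sample size or data collection is needed, and it can be done before any analysis.
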